### Maintenance (Provider Level): To What Degree and Time Point Did the *TEaM* Intervention Become Standard of Practice and Sustain Effectiveness?

Individual provider-level maintenance will be determined by utilization of the *TEaM* Intervention components and evidence-based practices in diagnosing and managing mTBI among HCPs 6 months following the end of the study period (36). To maintain the sustainability of the *TEaM* Intervention across sites and facilitate communication between HCPs and school personnel, engagement of stakeholders across delivery systems will be reinforced on mTBI best practices to promote patient recovery (25). Qualitative inquiry will complement data collection on individual level maintenance by understanding the barriers to sustainability of the *TEaM* Intervention across study sites (38). We will explore strategies to facilitate appropriate work-flow and practice changes and seek new sources of funding opportunities to help promote sustainability and scalability of the *TEaM* Intervention. Data sources will include site visits and interviews with site specific provider champions following the study period.

### Formative Evaluation

Formative evaluation of the *TEaM* Intervention will be guided by the RE-AIM QuEST Framework (38) as an expansion of RE-AIM (36) to inform qualitative data collection throughout each phase of the study period (Figure 1). To facilitate Adoption and Implementation, during study phase 1 (*Building a Foundation*), we will identify and assess stakeholder (providers, hospital administrators, IT system personnel) perceptions and feedback regarding the training and CDS tools, and anticipated implementation barriers and facilitators surrounding utilization of the *TEaM* Intervention components across delivery systems (ED, UC, PC). To facilitate Reach, during study phase 2 (*Provider Recruitment*), we will assess any barriers to recruitment and how these barriers were addressed (38). We will also assess provider knowledge and skills relating to mTBI diagnosis and management during recruitment and obtain provider feedback regarding the mTBI educational training modules. To facilitate Maintenance, at the completion of study Phase 3 (*Subject Enrollment and Pre-Decision Support*) and during study Phase 6 (*Study Wrap Up*) of the *TEaM* Intervention, we will evaluate provider experiences, perceptions, barriers, and facilitators regarding *TEaM* Intervention components across delivery systems. Reasons for adaptations to the *TEaM* Intervention components, and assessment of contextual factors underlying facilitators and barriers to implementation of the *TEaM* Intervention across delivery systems will be completed (38). Finally, we will evaluate provider, patient, family and school personnel experiences, perceptions, barriers, and facilitators regarding communication linkages across delivery systems. Qualitative data collection will include focus groups, formal meetings, semi-structured interviews, and surveys.

**Figure 1 F1:**
[figure not shown]
*TEaM* study timeline.

### Data Analyses

#### Sample Size

Sample size calculations were conducted with the aim of achieving 80% power for the primary outcome. Computations were based on previous research using the Concussion Learning Assessment and School Survey, 3rd Ed. (CLASS-3) which reported on the mean, variability, and intercorrelations for metrics derived from the CLASS (47). The sample size was calculated for a 1:1 treatment allocation scheme with 80% power to detect an overall 20% difference in the mean of the CLASS-3 Academic Problems Scale at the two-sided α level of 0.05 (corresponding to a Cohen's ≈ 0.15). With these parameters, we will randomize 532 patients after assuming a loss-to-follow-up rate of 20%. Assuming minimal loss-to-follow-up, power is expected to be ~88%.

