### Participants/Setting

Participants in this study include HCPs in ED, UC, and PC settings affiliated with Children's Healthcare of Atlanta. HCPs will include Physicians and Advanced Practice Providers (nurse practitioners and physician assistants). HCP level randomization will be stratified by practice site to ensure that the distribution of control and intervention providers is approximately equal within sites. Providers will be sent an electronic informed consent form (eICF) using Research Electronic Data Capture (REDCap™) tools (52) for consent to participate.

Children ages 5–18 years old who screen positive and/or are diagnosed with mTBI/concussion will be recruited following discharge from their index injury visit, which may have occurred in either ED, UC or PC settings. Regular reports of children who screen positive through the decision support tool will be sent to the research team throughout the 32-month study period. After confirmation of an evaluation by a participating provider and either a positive screen or diagnosis of mTBI/concussion, an initial phone call will be made to the parent.

Upon the first contact, the parent will be given a very brief explanation of the study at which point, an option to opt-out will be offered. If they choose to opt-in, a simple validated symptom questionnaire, the CDC Acute Concussion Evaluation (ACE) tool (45) will be used to ensure that the child meets eligibility requirements. At this point, if the child is eligible, parental verbal consent will be obtained in order to proceed with further explanation of the study. A total of 532 consecutive children (see section Data Analyses) with mTBI meeting inclusion/exclusion criteria will be recruited. The goal is to maintain a lost to follow up (LTF) rate of <20% for a total sample of 425. Enrolled children will be treated for up to 6 months post-injury to assess the impact of the *TEaM* Intervention on pediatric mTBI-related outcomes.

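### The stated Cohen index of about 0.15 does not reproduce the stated 80% power at 425 patients or 88% at 532 from the inputs printed with it

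*Protocol article*

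**What the plan says.** All the figures come from the protocol article.

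- **Aim (Sample Size):** "Sample size calculations were conducted with the aim of achieving 80% power for the primary outcome".
- **Design inputs (Sample Size):** "The sample size was calculated for a 1:1 treatment allocation scheme" and "at the two-sided α level of 0.05".
- **Effect (Sample Size):** the trial is sized "to detect an overall 20% difference in the mean of the CLASS-3 Academic Problems Scale", which the section glosses as "corresponding to a Cohen's ≈ 0.15". It gives no mean or standard deviation. It says only that the mean, variability and intercorrelations came from a cited study of the instrument.
- **Enrolment (Sample Size):** on the parameters listed, "we will randomize 532 patients after assuming a loss-to-follow-up rate of 20" per cent.
- **Evaluable number (Participants/Setting):** loss below 20% "for a total sample of 425".
- **Power without loss (Sample Size):** "Assuming minimal loss-to-follow-up, power is expected to be ~88" per cent.

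The section on the primary outcome plans a mixed-effects linear model over weeks 1, 2 and 4, with allowance for clustering by provider and patient. The sample-size text states no intracluster correlation, design effect or between-visit correlation.

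**The concern.** The section prints an effect size, a sample size and two powers as one derivation, so a reader should be able to get from one to the others. A standardised difference of 0.15 is small, and a two-group comparison of means would need well over a thousand patients to detect it with 80% power. If the index is Cohen's f, 0.15 corresponds to a standardised difference of 0.30, and 425 patients are more than enough.

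This is the justification for the primary analysis. As printed, it does not tell the reader whether the trial has about a one-in-three chance of detecting its target effect or close to nine in ten.

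**Working it through.** **Inputs.** Two-sided α = 0.05 (z = 1.96), power 80% (z = 0.8416), 1:1 allocation, N = 425 evaluable and N = 532 enrolled, index 0.15. All are from the article. Where a between-visit correlation or a design effect appears below, it is an assumption.

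**1. Loss to follow-up.** 425 / 0.8 = 531.25, rounded up to 532. This reproduces.

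**2. What the sample sizes and powers imply.** For two equal groups, the d detectable with 80% power is 2 × (1.96 + 0.8416) / √N. With N = 425 this is 5.603 / 20.616 = 0.272, or f = d/2 = 0.136. At N = 532 the same d gives a noncentrality of 0.272 × √532 / 2 = 3.13 and a power of 88%. So 425, 532, 80% and 88% are mutually consistent. The 0.15 is the figure that does not fit.

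**3. Read as d = 0.15, single score.** n per arm = 2 × (1.96 + 0.8416)² / 0.15² = 698, or 1,396 evaluable. Noncentrality is 0.15 × √N / 2, which is 1.546 at 425 and 1.730 at 532. Power is 34% and 41%. The noncentral t gives the same to the nearest point.

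**4. Read as d = 0.15, mean of the three visits.** The variance is multiplied by (1 + 2ρ)/3.

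| Assumed ρ | Power at 425 | Power at 532 |
|---|---|---|
| 0.7 | 41% | 49% |
| 0.5 | 47% | 56% |
| 0.3 | 56% | 66% |
| 0 | 76% | 85% |

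Reaching 80% at 425 needs a factor of (0.15/0.2718)² = 0.305. The smallest value possible with a non-negative correlation is 1/3, so no such correlation is enough. Any clustering by provider that inflates the variance lowers these figures.

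**5. Read as f = 0.15 (d = 0.30), one degree of freedom, no clustering.** n per arm = 2 × (2.8016)² / 0.30² = 175, or 350 evaluable. Noncentrality is 3.09 at 425 and 3.46 at 532. Power is 87% and 93%. Averaging visits moves it further from the stated values (97% at 425 with ρ = 0.5).

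**6. Rounding of 0.15.** d = 0.155 gives 36% and 43%. f = 0.145 gives 85% and 92%. Neither reaches 80% and 88%.

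**7. Unstated inputs that would reconcile f = 0.15.** The design effect needed is (0.30/0.2718)² = 1.22.

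| Added input | Power at 425 | Power at 532 |
|---|---|---|
| Design effect 1.20 | 81% | 88% |
| Design effect 1.22 | 80% | 88% |
| F test on 2 df, noncentrality f²N | 79% | 88% |

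**The case against.** The strongest objection is that 0.15 may be correct. The symbol after the name of the index may have been lost when the text was extracted, so its absence is not a fault. If the index is f, a design effect of about 1.2 reproduces both 80% and 88%. The article plans a model that accounts for clustering by provider, so such an allowance would be unsurprising. An F test on two degrees of freedom, as a group-by-time term over three visits would produce, also fits. The mention of intercorrelations suggests that the calculation was not the simple single-score formula, and an article may leave such inputs to the full protocol.

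Much of this stands. A reader might infer that the trial is underpowered, or that the 20% difference, the 0.15 and the 532 cannot all be true. The documents support neither inference: nothing in them favours d over f, and f with one ordinary extra input closes the gap. For the same reason it would be wrong simply to replace 0.15 by 0.27, because that could overwrite a correct value.

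The objection does not remove the mismatch itself. The section presents 532 as following from the parameters it lists, and neither a design effect nor a two-degree-of-freedom test is among them. A 1:1 comparison of an overall difference in means points to one degree of freedom, which makes the second route the weaker. Leaving out the mean and standard deviation would be ordinary condensation. Printing an effect size and powers that disagree on the inputs shown is a different matter.

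**Conclusion.** The point holds as a mismatch in the printed derivation, at moderate severity. Under neither usual reading does 0.15 give the stated 80% and 88% from the stated inputs. As d the powers are 34% and 41% (47% and 56% for three visits at an assumed correlation of 0.5). As f on one degree of freedom without clustering they are 87% and 93%.

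The sign of the discrepancy depends on the index. A loss of power is established only for d. For f the trial either exceeds 80% or, with an allowance the article does not state, meets it. The calculations assume equal groups and a normally distributed test statistic. The d and one-degree-of-freedom f figures also assume no clustering.

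**What to change.** Keep the enrolment target. In the Sample Size section, state the index, the test and any clustering allowance behind 532. Then:

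- **If 0.15 is d:** restate the power, or replace 0.15 with the value that 425 and 532 support (about 0.27 on the analysed score with no clustering allowance) and confirm that it corresponds to a 20% difference in the mean.
- **If 0.15 is f with a clustering allowance or a two-degree-of-freedom test:** state that allowance or test, so that 80% and 88% follow.
- **If 0.15 is f with neither:** correct the index to about 0.136, or restate the power as about 87% and 93%.

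The cost is a sentence or two of text. In the d case the stated power may have to be much lower.

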## Methods

### Study Design Overview

The *TEaM* study is a combined randomized and 2 × 2 quasi-experimental study design with training and technology interventions occurring at the provider level involving ED, UC, PC healthcare providers (HCPs) across the Children's Healthcare of Atlanta system, with patient and school outcomes as key endpoints. At the HCP level, this study is randomized, and at the patient level, this study is a quasi-experimental with a pre and post design to facilitate analysis of the impact of our Electronic Medical Record (eMR) support tool on children's health outcomes.

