#### Primary Outcome—CLASS-3 Academic Problems Scale

Analyses will be conducted under the intention-to-treat principle (ITT). Scores on the CLASS-3 Academic Problems scale (42 pt. scale) will be compared between intervention and control patients using a mixed-effects/multilevel linear regression. Experimental group and Timepoint (weeks 1, 2, and 4) will be included as independent variables. The mixed-effects model will be used in order to account for clustering within the data (e.g., clustering within provider, patient, etc.). When possible, the intercept and intervention slope will be included as random effects to evaluate the variability between providers and sites. Alternatives will be considered if model assumptions are not met or if the model fails to estimate properly.

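### The sample size is described as if 532 patients were randomised individually, although providers are randomised; the stated 80% and roughly 88% power are not shown to hold for that design.

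*Protocol article*

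**What the plan says.** The protocol article gives two accounts of what is randomised.

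- **Study Design Overview:** "At the HCP level, this study is randomized, and at the patient level, this study is a quasi-experimental" comparison with a pre/post element.
- **Participants/Setting:** "HCP level randomization will be stratified by practice site", so that the arms are balanced within sites. The 532 children are described here as recruited, with 425 expected after losses.
- **Sample Size:** "The sample size was calculated for a 1:1 treatment allocation scheme". The target is "80% power to detect an overall 20% difference in the mean of the CLASS-3 Academic Problems Scale", tested two-sided at 0.05; the section equates this difference with a Cohen's index of about 0.15. It continues: "With these parameters, we will randomize 532 patients after assuming a loss-to-follow-up rate of 20" per cent. With minimal loss, power is put at about 88%.

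The only correlations mentioned in Sample Size are those among CLASS metrics, taken from earlier research. The Primary Outcome section then says "The mixed-effects model will be used in order to account for clustering within the data", and names provider as one level of clustering, with a random intercept and intervention slope where possible.

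**The concern.** Under the design sections no patient is randomised; a child's arm follows from the provider seen. Patients of one provider share that provider's training, habits and case mix, so their outcomes may be correlated. If so, 425 patients carry less information than 425 independent ones.

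The listed inputs are allocation ratio, power, mean difference, alpha and loss to follow-up. Number of providers, patients per provider, ICC and design effect are not among them. The analysis model will charge for between-provider variance that the stated power does not mention. If nothing was allowed for it, a null result would be read against more power than the trial has.

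**Working it through.** **Inputs from the article.** Two-sided alpha 0.05; 80% power; 1:1 allocation; 532 enrolled; 20% loss; 425 analysed; about 88% with minimal loss; a 20% mean difference; a Cohen's index of about 0.15 whose letter is not printed. No mean, SD, number of providers or ICC is given.

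**1. Loss to follow-up reproduces.** 425 / 0.8 = 531.25, rounded up to 532.

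**2. The step from 80% to 88% reproduces with independent patients.** 80% power means a noncentrality of 1.96 + 0.84 = 2.80. At 532 it is 2.80 × √(532/425) = 3.13, and Φ(3.13 − 1.96) = 88.0%.

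**3. The 425 does not reproduce from 0.15** (normal approximation, two equal arms).

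- If 0.15 is d: 1396 patients are needed for 80% power, and power is 34% at 425 and 41% at 532. Averaging the three visits with zero within-patient correlation would still need 466.
- If 0.15 is f (d = 0.30): 350 are needed, and power is 87% at 425 and 93% at 532.
- The d detectable with 80% power at 425 is 2.80 × √(4/425) = 0.272, which matches neither.

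**4. Could 425 already contain an allowance?** Under the f reading, 425 / 350 = 1.21. With d = 0.30 and a constant variance inflation of 1.21, the noncentrality at 425 is 0.30 × √(425/4) / √1.21 = 2.81, giving 80.3%. At 532 it is 0.30 × √(532/4) / √1.21 = 3.15, giving 88.2%. So the two stated powers also fit a constant unstated inflation. They fit less well if providers are fixed and better retention means more patients for each: starting from 80% at 425 with clustering included, 532 gives 86.3% (5 per provider, ICC 0.05) or 85.2% (10, 0.05).

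**5. Illustration if the 80% at 425 is unclustered.** Assumed: m patients per provider at 425, equal cluster sizes, and the same providers at 532, so that m rises to m × 532/425. The design effect is DE = 1 + (m − 1) × ICC. Power is Φ(2.80 × √(N/425) / √DE − 1.96). The detectable difference at 425 is 20% × √DE.

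| m at 425 (implied providers) | ICC | DE at 425 | Power at 425 | DE at 532 | Power at 532 | Detectable difference at 425, % of mean |
|---|---|---|---|---|---|---|
| 2 (about 212) | 0.01 | 1.01 | 79.6% | 1.015 | 87.5% | 20.1 |
| 5 (85) | 0.01 | 1.04 | 78% | 1.053 | 86% | 20.4 |
| 5 (85) | 0.05 | 1.20 | 72% | 1.263 | 80% | 21.9 |
| 10 (about 42) | 0.05 | 1.45 | 64% | 1.576 | 70% | 24.1 |
| 20 (about 21) | 0.05 | 1.95 | 52% | 2.202 | 56% | 27.9 |

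Worked row (5, 0.05): at 425, 2.80 / √1.20 = 2.56 and Φ(2.56 − 1.96) = 72%. At 532, m = 6.26, DE = 1 + 5.26 × 0.05 = 1.263, and power is 80%.

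**The case against.** This is a condensed article. Number of providers, cluster size and ICC are inputs that a full protocol or analysis plan may hold, so their absence here does not prove that they were ignored. A reader might infer that the 80% and 88% contain nothing for provider clustering. The document does not support that: 425 cannot be derived from the printed effect size, and step 4 shows that a constant inflation near 1.21 would give both stated powers. In that case the losses in the table would count clustering twice. This part of the objection stands.

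It also stands that the loss may be small. Providers come from emergency, urgent and primary care across a whole health system, so few patients per provider is plausible, and a provider ICC for school problems reported by parents and students may be low. The simple design effect further leaves out the three visits, stratification by site, the pre/post structure and the covariates. The planned test models provider clustering, so the issue lies in the stated power and design description.

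Condensation does not explain the sentence itself. It names patients as the randomised unit, against two other sections, and attributes 532 to a list of inputs none of which concerns providers.

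**Conclusion.** The point holds in this form. The Sample Size section describes an individually randomised trial, which contradicts the provider randomisation stated elsewhere; that needs no assumption. The inputs credited for 532 include no allowance for a clustering that the primary model expects, so the stated 80% and roughly 88% are not established for this design. The step between them is what independent patients would give, which suggests an unclustered calculation without proving one.

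The size is conditional. If the 80% at 425 is unclustered, the loss runs from negligible (79.6% at 2 patients per provider, ICC 0.01) to serious (52% at 20, ICC 0.05), and the detectable difference grows from 20% to between about 20% and 28% of the mean. These figures rest on assumed ICCs and cluster sizes, equal clusters and a fixed set of providers. If 0.15 is d, the stated 80% has no valid base even before clustering, so the effect-size index must be settled first.

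**What to change.** 1. Replace the sentence on randomising 532 patients with: *providers are randomised 1:1 within site and 532 of their patients enrolled*.
2. Name the effect-size index behind 0.15, and show how it and the 20% mean difference lead to 425.
3. Restate power and detectable difference at 425 and 532 analysed, using the expected number of providers, unequal cluster sizes and an ICC range, for example DE = 1 + (m(1 + CV²) − 1) × ICC, where CV is the coefficient of variation of patients per provider. Let m rise between 425 and 532, since better retention adds patients to the same providers.
4. If 425 already includes an allowance for clustering, state its size and source instead.

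Keep 532. No patients are added and the primary model does not change; the cost is a short recalculation and probably less favourable power figures. The Project Status section says that the interventions requiring provider enrolment are still being developed, so expected provider numbers can be set down before outcomes are read against the stated power.

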#### Descriptive Statistics

Frequencies and percentages will be used to describe categorical variables. Means, standard deviations, medians, and interquartile ranges will be used to describe continuous variables. The reliability of variables obtained via chart review will be evaluated using intraclass correlations, Cohen's κ, or Fleiss' κ depending on the characteristics of the variable.

#### Primary Outcome—CLASS-3 Academic Problems Scale

Analyses will be conducted under the intention-to-treat principle (ITT). Scores on the CLASS-3 Academic Problems scale (42 pt. scale) will be compared between intervention and control patients using a mixed-effects/multilevel linear regression. Experimental group and Timepoint (weeks 1, 2, and 4) will be included as independent variables. The mixed-effects model will be used in order to account for clustering within the data (e.g., clustering within provider, patient, etc.). When possible, the intercept and intervention slope will be included as random effects to evaluate the variability between providers and sites. Alternatives will be considered if model assumptions are not met or if the model fails to estimate properly.

#### Secondary Outcomes—(PCSI Emotion Scale, PCEI Emotional Control Scale, CLASS-3 School Stresses Scale, PEDS QL4, Time to Recovery)

For continuous variables, the analyses will be the same as above: either a mixed-effects/multilevel linear regression. For other variables, the distribution family and link function will be determined by the characteristics of the data.

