## Introduction

Mild Traumatic Brain Injury (mTBI) is a considerable public health problem that is responsible for more than 70% of traumatic brain injuries in the United States (1, 2). Between 2004 and 2013, head injury among children up to 17 years of age accounted for 1.6 million outpatient (68%) and Emergency Department (ED) (32%) visits (3). In 2014 alone, TBI-associated ED visits, hospitalizations, and deaths comprised more than 837,000 children (4).

Children who sustain an mTBI may be seen in multiple healthcare settings across their recovery, such as primary care, urgent care, specialty clinics, ED, and inpatient settings (5, 6), while most of the recovery phase occurs in the home and school settings (5). Unfortunately, inconsistency in management approaches and treatment recommendations exist across the various healthcare settings (5, 7). Adding to this complexity is the reality that communication linkages between the healthcare systems and the schools are frail. As a result, this lack of communication and care coordination increases the risk of re-exposure to mTBI, less effective management in healthcare settings, and delayed recovery (5).

Current needs and opportunities for improvement exist in the management of mTBI in children, explicitly traversing across the care continuum from emergency and urgent care to primary care settings and then to the schools where the child spends a significant amount of their day. Therefore, we view the ecology of mTBI services as akin to a neighborhood, with various elements that must work together to be a successful community.

A growing number of studies offer insight into the consequences of mTBI (8–13). Children who sustain a TBI, including mTBI, may encounter cognitive and behavioral changes that can negatively influence school performance (13–16). These changes may even influence the quality of life in childhood and adult years (8, 17, 18). For most children who experience symptoms related to mTBI, recovery typically occurs between 1 and 6 weeks (19–21); however, symptoms can persist up to 3 months or longer following injury (10, 17, 21, 22).

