### Effectiveness/Efficacy (Patient Level): How Effective Is the *TEaM* Intervention at Improving mTBI-Related Outcomes, Including Academic Performance and Health-Related Quality of Life Among School-Aged Children With Concussions?

The primary outcome of the *TEaM* Intervention is to determine if implementation of an evidence-based/best practice mTBI intervention with multi-setting communication linkages will decrease mTBI-related complications among school-aged children, a universal endpoint. Effectiveness of the intervention for the intervention group vs. controls (38) will be examined on important patient level outcomes utilizing validated instruments. The primary outcome is degree of academic problems as reported by the parent and student on the Concussion Learning Assessment and School Survey, 3rd Ed (**CLASS-3**) (14, 47). Secondary outcomes will be the emotional responses of the students as measured by the Emotional Symptom scale of the PostConcussion Symptom Inventory-2 (**PCSI-2**) (48), the Emotional Control scale of the PostConcussion Executive Inventory (**PCEI**) (49), and the School Stresses scale of the CLASS-3. General well-being will be assessed by the Pediatric Quality of Life Inventory (**PEDS QL4**) (50, 51). Each of these measures will be administered at 1, 2, 4, and 12 weeks. Finally, time to recovery (45, 46) will be assessed for each study group. Attrition rates of patients will also be determined. Further data collection will include qualitative inquiry on effectiveness. Our objective is to determine the circumstances and processes that resulted in *TEaM* Intervention effectiveness and the differences in patient-level outcome measures across study sites (38). Data sources will include eMR, surveys, telephone interviews with patients and parents.

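### Time to Recovery is placed under a linear or family-and-link rule that says nothing about children whose recovery is never observed; a linear analysis would shrink a real difference

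*Protocol article*

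**What the plan says.** The relevant heading under Data Analyses reads "Secondary Outcomes—(PCSI Emotion Scale, PCEI Emotional Control Scale, CLASS-3 School Stresses Scale, PEDS QL4, Time to Recovery", so time to recovery is explicitly covered by the text beneath it. That text has two parts. The first is "For continuous variables, the analyses will be the same as above: either a mixed-effects/multilevel linear regression". The second is "For other variables, the distribution family and link function will be determined by the characteristics of the data".

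The model referred to as being above is the one for the CLASS-3 Academic Problems scale: a mixed-effects linear regression on group and timepoint, with the fallback "Alternatives will be considered if model assumptions are not met or if the model fails to estimate properly".

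On the endpoint itself, the Effectiveness/Efficacy section says only "Finally, time to recovery (45, 46) will be assessed for each study group". Just before that, it says of the questionnaires: "Each of these measures will be administered at 1, 2, 4, and 12 weeks". Table 1 lists time to recovery as a secondary outcome without assessment weeks.

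Three other statements matter:
- The Introduction says that "symptoms can persist up to 3 months or longer following injury".
- Participants/Setting aims for less than 20% loss to follow-up (532 recruited, 425 retained).
- Missing Data offers multiple imputation, of a type to be decided later, if missing data are substantial. Its worst-case and best-case assignments concern the primary CLASS-3 score only.

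**The concern.** Elapsed time is most naturally read as a continuous variable, which sends it to the linear model. That model does not fit well even before censoring is considered: it is built for scores repeated at visits, with timepoint as a predictor, whereas a child has one recovery time.

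The larger difficulty is that some children will have no observed recovery time. A child still symptomatic at week 12 is not simply missing, because the recovery time is known to exceed 12 weeks. A child lost at week 3 while symptomatic is known to exceed 3 weeks. A linear model of observed times has no term for this partial information. Such children must be dropped or given a value, and the article does not say which.

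If they are dropped, the slowest recoverers go, and more of them go from the arm with slower recovery. The difference then shrinks. The endpoint is one of the secondary outcomes under formal false discovery rate control (Multiple Testing), and better symptom recovery is a stated aim of the intervention. An attenuated estimate, from a model chosen after the data are seen, would weaken that evidence.

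**Working it through.** **The plan's own figures.** The article gives no number for time to recovery, so there is none to reproduce. The one planning input used here, loss, is consistent: 532 × 0.80 = 425.6, against the stated 425.

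**Inputs.** From the article: visits at weeks 1, 2, 4 and 12, and loss of up to about 20%. Assumed: recovery hazard ratio 1.4; share of controls unrecovered at week 12, p = 0.30, 0.20 or 0.10; Weibull recovery times with shape k = 0.7, 0.8 or 1.0 respectively.

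**A. Unrecovered children dropped, all times on the visit scale.**

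Control probability of being unrecovered at week t: Sc(t) = p^((t/12)^k). Intervention: Si(t) = Sc(t)^1.4.

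Restricted mean to 12 weeks, with recovery assigned to the next visit: RM = 1 + S(1) + 2·S(2) + 8·S(4).

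Mean among recovered children: M = (RM − 12·S(12)) / (1 − S(12)).

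For p = 0.30:
- Control: S = 0.809, 0.709, 0.572, 0.300 at weeks 1, 2, 4, 12. RM = 7.81; M = (7.807 − 3.600)/0.700 = 6.01.
- Intervention: S = 0.744, 0.618, 0.458, 0.185. RM = 6.64; M = (6.643 − 2.224)/0.815 = 5.42.
- Difference in RM: 1.16 weeks. Difference among recovered: 0.58 weeks. Attenuation: 1 − 0.58/1.16 = 50%.

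| Controls unrecovered at week 12 | RM difference (weeks) | Difference among recovered (weeks) | Attenuation |
|---|---|---|---|
| 30% | 1.16 | 0.58 | 50% |
| 20% | 1.22 | 0.74 | 40% |
| 10% | 1.24 | 0.93 | 25% |

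A separate simulation used exponential times observed continuously, hazard ratio 1.3 and 20% loss per arm. Recoveries-only differences against the 12-week restricted mean differences were 0.50 against 0.63 weeks (control median 2 weeks), 0.45 against 0.91 (median 4) and 0.36 against 0.94 (median 6). The events-per-person-time hazard ratio stayed at 1.30 in all three.

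**B. Last contact counted as recovery, equal loss.** With 20% loss spread uniformly over 12 weeks, the chance of still being in follow-up at t is G(t) = 1 − 0.20·t/12. The estimated difference is the integral of (Sc − Si)·G, against the integral of (Sc − Si) for the true restricted mean difference. As G never falls below 0.80, the attenuation cannot exceed 20% when Si stays below Sc. In the Weibull settings above, on continuous times, the differences are 1.15 against 1.29, 1.13 against 1.26, and 1.01 against 1.11 weeks: 10-11%. The exponential settings give 0.58 against 0.63, 0.81 against 0.91, and 0.83 against 0.94: 8-12%.

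**C. No true effect, unequal loss (25% and 15%), last contact counted as recovery.** The false difference is the integral from 0 to 12 of S(t)·(0.10·t/12). For exponential times with median 4 weeks, λ = ln 2/4 = 0.1733, and the integral of t·exp(−λt) is [1 − 0.125 × (1 + 2.079)]/0.03003 = 20.5. The false difference is 20.5 × 0.10/12 = 0.17 weeks; simulation gave 0.17-0.18. The arm with more loss looks faster. With no effect and equal loss there is no bias.

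**The case against.** The strongest reply is that the rule does not exclude a proper analysis. A discrete-time model with a complementary log-log link is a binomial mixed model fitted to one row per child per interval, so the family-and-link sentence could admit it. The primary model's fallback also allows alternatives. This stands: a reader might infer that the plan rules out handling censoring, and the text does not support that. But choosing a family and link does not by itself create the person-period data or the censoring rule, and nothing in the article points that way.

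Second, this is a condensed article, and the details of a secondary outcome may sit in an analysis plan not shown. That would answer a complaint that detail is missing. It does not fully answer this one, because the article names the endpoint and assigns it a rule whose natural reading is unsuitable.

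Third, the article nowhere says that unrecovered children will be dropped or last contact treated as recovery. Correct, so the bias is conditional. Entering 12 weeks for a child followed to week 12 and still unrecovered reproduces the restricted mean and causes no bias; only earlier loss then matters.

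Fourth, a reader might infer that recovery is seen only at the four visits. That is not established. The sentence on visit weeks precedes the one on time to recovery, Table 1 gives the endpoint no weeks, and the data sources include the medical record and telephone interviews. Recovery dates may be recorded.

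**Conclusion.** The concern holds in a conditional form. Time to recovery is put under a rule that makes no provision for children unrecovered or lost at last contact, whom the article itself expects. Read as a continuous variable in a linear model, the endpoint would give an attenuated difference when a true effect exists: roughly 25-50% in the visit-based illustration if unrecovered children are dropped, and about 10% if last contact counts as recovery with 20% equal loss. Unequal loss can produce a small false difference.

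The sizes rest on the assumed hazard ratio, recovery distribution and loss pattern, since the article supplies no recovery distribution. The bias is smaller if most children recover within about two weeks. It would be too strong to say that the recovery result will be biased, or that about half the effect will be lost: the first depends on handling the article does not state, and the second applies only to dropping unrecovered children when many remain unrecovered.

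This is a secondary endpoint and the primary analysis is not affected. The change is still worth making, because it is cheap and removes a choice otherwise made after seeing the data.

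**What to change.** Take Time to Recovery out of the shared rule for secondary outcomes and give it its own short paragraph:

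- Define the recovery event and the time origin.
- Censor children not known to have recovered at their last contact. State the horizon, since the article gives a last scheduled assessment at 12 weeks but also mentions up to 6 months after injury.
- If recovery is known only at the week 1, 2, 4 and 12 contacts, use a discrete-time complementary log-log model with intervals 0-1, 1-2, 2-4 and 4-12 weeks, a provider random intercept, and site.
- If recovery dates are recorded, use a Cox model with provider frailty or cluster-robust variance, and site.
- Report the hazard ratio and the restricted mean time to recovery up to 12 weeks, by group, with the number censored and why.

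The cost is wording and standard code. No new data or visits are needed.
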